## Abstract

Insomnia is a common problem for individuals with multiple sclerosis (MS) occurring in at least 40 % of individuals with MS. Sleep disturbances in people with MS have been associated with a reduction in cognitive performance, physical function, psychological well-being, quality of life, and occupational function, as well as increased prevalence of fatigue, pain, depression, and anxiety. Cognitive behavioral therapy for insomnia (CBT-I), a multicomponent treatment strategy, addresses thoughts and behaviors that can negatively impact sleep and is the recommended treatment for chronic insomnia. CBT-I is shown to be more effective than pharmacological interventions long-term for treating insomnia with improvements remaining up to 10 years following CBT-I. However, there are limited studies that have examined the effect of CBT-I on sleep outcomes and comorbid symptoms in people with MS. The objective of the proposed study is to determine the efficacy of CBT-I delivered via telehealth to improve insomnia symptoms, fatigue, and health-related quality of life in people with MS. CBT-I offers a low-risk, cost-effective, non-pharmacological approach to improving sleep quality, fatigue, and daily functioning in individuals with MS. Targeting insomnia in MS may also reduce disability, enhance quality of life, increase employment rates, and lower healthcare and support costs. Furthermore, understanding factors that impact improvement in outcomes will allow more accurate individualization of insomnia treatment for people with MS.

**Trial registration:**

The CALM study is registered at: https://clinicaltrials.gov (NCT06428006).

## Introduction

1

Insomnia is a significant concern for many individuals with multiple sclerosis (MS). A diagnosable sleep disorder occurs in approximately 50 % of individuals with MS, with up to 70 % reporting sleep disturbances [1,2]. Moreover, chronic insomnia, defined as difficulty falling asleep, maintaining sleep, or waking up too early at least 3 nights/week over the past 3 months [3], is experienced by 40 % or more of individuals with MS [4]. However, the incidence of insomnia is likely higher. One study found that only 11 % of people with MS (pwMS) who screened positive for moderate-to-severe insomnia reported being diagnosed by a health care provider [5]. Insomnia is broadly linked to reduced cognitive performance, impaired psychological well-being, and lower occupational and interpersonal functioning [6]. In pwMS, sleep disturbance compounds MS-related challenges, contributing to greater difficulties in physical functioning and activities of daily living (ADLs), heightened fatigue and pain, and more pronounced mood symptoms, ultimately lowering quality of life [[7], [8], [9], [10], [11]].

Fatigue is the most common symptom in pwMS, reported in up to 90 % of individuals [12]. In 40 % of pwMS, fatigue is reported as the worst symptom [13]. Fatigue contributes to reduced quality of life, unemployment, and decreased participation in ADL's in pwMS [14,15]. No pharmacological interventions have strong evidence for improving MS-related fatigue [16]. Not surprisingly, sleep disturbances have been associated with an increase in perceived fatigue in pwMS. A previous case series performed by Clancy and colleagues demonstrated that a cognitive behavioral therapy protocol effectively improves fatigue outcomes in pwMS [17]. These findings highlight the potential for behavioral interventions to reduce fatigue in pwMS.

Cognitive Behavioral Therapy for Insomnia (CBT-I) is a multicomponent treatment strategy that addresses behaviors and thoughts that negatively impact sleep and is the recommended treatment for chronic insomnia [18]. CBT-I improves sleep efficacy and sleep latency, reduces awakenings after sleep onset, and increases total sleep time in people with insomnia [19,20]. Furthermore, compared to pharmacological interventions, CBT-I has been shown to be more effective long-term for treating insomnia [21]. Importantly, improvements in sleep outcomes remain up to 10 years following CBT-I [22]. Prior economic evaluations consistently demonstrate that CBT-I yields favorable cost-effectiveness ratios, driven by durable symptom improvement and reductions in healthcare utilization [23]. In addition, recent meta-analyses [18,24] determined that CBT-I produced medium to large effect sizes on sleep outcomes in people with a variety of comorbid conditions. However, pwMS do not appear to have participated in any of the studies included in the meta-analyses [18,24].

While CBT-I is a first-line recommended behavioral intervention for insomnia according to guidelines from the American College of Physicians [25], the European Sleep Research Society [26], and the American Academy of Sleep Medicine [27], there are limited studies that have examined the effect of CBT-I on sleep outcomes and comorbid MS symptoms. We recently completed the first pilot randomized controlled trials to assess feasibility and preliminary efficacy of CBT-I modified specifically for pwMS [28,29]. Modifications that we made to the standard CBT-I program include: 1. For individuals who felt a nap was necessary for their health and wellbeing, the recommendation to avoid naps was modified to limit napping to ≤30 min, to take the nap as early in the day as possible, and delaying bedtime to a later time may be necessary until they were adequately tired; 2. For individuals with functional or mobility limitations or those who had concerns about falls (either individual or CBT-I provider), stimulus control was modified to perform a relaxation or distraction technique in bed; 3. For individuals who were concerned that the contraction portion of progressive muscle relaxation (PMR) might exacerbate spasticity (despite the standard instruction to gently tense muscle groups without causing discomfort), PMR was modified to focus solely on the relaxation component (i.e., releasing tension) without performing the contraction phase.

Whereas our pilot studies demonstrate feasibility and a large effect on sleep outcomes in pwMS following CBT-I [28,29], a well-designed adequately powered prospective randomized control trial (RCT) is needed to assess the efficacy of CBT-I delivered via telehealth compared to an appropriate control group to improve sleep outcomes (Aim 1) and fatigue and health-related quality of life (Aim 2). Also, determining the participant characteristics that predict improvement in sleep outcomes (Exploratory Aim 3) would help guide health care providers and individuals with MS to select an appropriate sleep intervention at an individual level.

## Methods

2

### Study overview

2.1

This proposed study is a Phase II, prospective, randomized, controlled clinical trial to assess the efficacy of CBT-I in n = 70 individuals with MS (Fig. 1). Individuals meeting the inclusion/exclusion criteria are randomized to one-on-one CBT-I provided via HIPAA-compliant Zoom (CBT-I; n = 35) or active control via Zoom (Control; n = 35). The study was designed based on CONSORT criteria [30], including concealed allocation for the study coordinator who conducts screening and determines eligibility with confirmation by PI and independent, masked intention-to-treat data analysis by the biostatistician. Reassessment of outcomes is completed after the 6-week intervention and 6 months following completion of interventions.

**Fig. 1 fig1:**
[figure not shown]
Study design.

### Recruitment

2.2

Participants are recruited from: (1) the MS clinic at the University of Kansas Medical Center (KUMC) which serves approximately 3500 patients with MS, (2) through newsletters and emails distributed by the National Multiple Sclerosis Society to individuals across the United States, (3) newsletters distributed by the Accelerated Cure organization, (4) support groups, and (5) social media. Because this study is conducted completely remotely and with our prior recruitment collaboration with the National Multiple Sclerosis Society [28,31], we anticipate successful recruitment across the United States which will enhance generalizability of the results. Additionally, a social media campaign using targeted ad placement on Facebook is conducted in collaboration with the KUMC Office of Communications. This study is registered on clinicaltrials.gov (NCT06428006).

### Screening procedures

2.3

Potential participants undergo a standard phone screening process conducted by the study coordinator to determine eligibility.

Phone Screen:1.Standardized review of inclusion/exclusion criteria (Table 1).

**Table 1 tbl1:** Inclusion and exclusion criteria.

Inclusion Criteria	• 18–65 years old (upper age limit in place to reduce heterogeneity in sleep architecture changes due to aging) • Diagnosis of relapsing-remitting or secondary progressive MS based on established guidelines [56] and verified by their neurologist • Mild-to-moderately severe disability (≤6 on Patient Determined Disability Steps (PDDS) scale) [32] • Report of difficulty falling asleep, maintaining sleep, or waking up too early at least 3 nights/week for the past 3 months with significant distress and impact on function despite adequate opportunity for sleep and not due to other sleep disorders as indicated in the DSM-5 • ≥10 on Insomnia Severity Index [35] • English speaking • ≥ 31 on modified Telephone Interview of Cognitive Status [36] • Has a high school diploma or equivalent to serve as a proxy measurement of reading ability to ensure adequate reading ability to participate in the study • Report having access to internet service or a data plan and access to a computer, tablet, or smart phone
Exclusion Criteria	• Known untreated sleep disorder (such as sleep apnea or restless legs syndrome) • >3 on STOP BANG indicating increased risk of sleep apnea [37] • Restless legs syndrome as determined by RLS-Diagnosis Index [39] • Circadian rhythm sleep-wake disorder as determined by the Sleep Disorders-Revised [40] • Parasomnia as determined by the Sleep Disorders-Revised [40] • Currently taking benzodiazepines, non-benzodiazepines, or melatonin supplements or agonists for insomnia • Score of ≥20 on the Patient Health Questionnaire (PHQ-9) indicating severe depression or endorsement of suicidal ideation (answer 1, 2 or 3 on #9 of the PHQ-9) [41] • Score of ≥15 on the Generalized Anxiety Disorder (GAD-7) indicating severe anxiety [42] • Current or history (up to 2 years) of alcohol or drug or alcohol abuse as indicated by DSM-5 criteria • History of other nervous system disorder such as stroke or Parkinson's disease • Currently pregnant or intending to become pregnant in the next 6 months. • Severe mental illness such as schizophrenia or bipolar disorder • Severe neurological or sensory impairments that would interfere significantly with testing • Relapse and/or corticosteroid use in the past 8 weeks • History of (within 5 years) or currently conducting overnight shift work including hours of midnight-4am • Currently receiving a behavioral sleep health intervention2.Disability will be assessed by the Patient-Determined Disability Steps (PDDS) [32] scale which is a single-item 9-point scale ranging from “normal” (score of 0) to “bedridden” (score of 8). The PDDS has been validated and highly associated with the Expanded Disability Status Scale [33]. A score of ≤6 is considered mild-to-moderately severe disability.3.The Insomnia Severity Index (ISI) [34] which is a valid and reliable measure of insomnia severity and consists of 7 questions each rated on a 0–4 scale. The range of scores on the ISI is 0–28, with ≥10 suggesting clinical insomnia [35].4.The 13-item modified Telephone Interview of Cognitive Status (TICS-M) [36] will be used to determine global cognitive status. A score 31 or greater will be considered non-demented [36].5.The 8 item STOP BANG [37] will be used to assess for risk of obstructive sleep apnea. A score of >3 is highly sensitive in detecting obstructive sleep apnea in various patient groups [38].6.The RLS-Diagnosis Index [39] will be used to screen for restless legs syndrome.7.The Structured Clinical interview for Sleep Disorders-Revised (SCISD-R) [40] will be used to screen for presence of circadian rhythm sleep-wake disorders and parasomnias.8.Depressive symptoms will be assessed using the 9-item Patient Health Questionnaire (PHQ-9), with a score of ≥20 suggesting severe depression [41].9.Anxiety symptoms will be assessed using the 7-item Generalized Anxiety Disorder (GAD-7), with a score of ≥15 indicating severe anxiety [42].

### Baseline evaluation

2.4

Eligible individuals are emailed a link to complete the consent document and baseline assessment questionnaires using the Research Electronic Data Capture (REDCap) web-based, electronic data capture tools hosted on a secure, HIPAA compliant server at KUMC [43]. Participants are mailed the actigraph (wGT3X-BT®, LEAP ®, ActiGraph corp. Pensacola, FL) and instructed to wear the actigraph on their non-dominant wrist for 7 days and nights. Baseline assessment is completed within 2 weeks of screening. It is important to note that actigraphy is known to underestimate sleep onset latency (delayed sleep onset is one characteristic of insomnia), and there are inconsistent results in studies that attempted to use actigraphy to distinguish between those with and without insomnia. Therefore, actigraphy is not a valid assessment of insomnia and is not used as an inclusion/exclusion criterion. However, actigraphy is sufficiently sensitive to detect changes in sleep patterns modified by CBT-I and is a well-used assessment of intervention efficacy. Using actigraphy in combination with self-report assessments provides a more robust assessment of change in sleep due to CBT-I.

*Allocation concealment:* To reduce the risk of bias, the research assistant who completes actigraph analyses is unaware of the condition to which participants were randomized. While participants are aware of the group they are randomized into, they are informed that the purpose of the study is to determine the effect of two different interventions on sleep to reduce the impact of expectation bias.

*Randomization:* Participants were randomized using a permuted block randomization scheme with a fixed block size of 10 to ensure balance between groups over time. A random/pseudo-random number generator was used in SAS v9.4 to develop the randomization list. The study biostatistician wrote the program code in SAS to derive and maintain this list. The randomization list is securely stored on the study coordinator's password-protected computer, inaccessible to the research assistant conducting assessments. Following completion of baseline assessments, the study coordinator conducts informs the participants of their assigned study arm via a scheduled phone call and documents group assignment in REDCap for study tracking.

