### Sample size justification

3.1

We will enroll 70 participants (35 in each of the two groups) in our study. Our sample size calculations are guided by effect size estimates for the primary outcome of ISI and PSQI from our pilot studies [28,29]. We hypothesize that CBT-I will perform better than the Control group for ISI and PSQI. Our hypotheses are – $H_{0}:\mu_{CBT-I}\leq \mu_{Control}$ vs $H_{0}:\mu_{CBT-I}>\mu_{Control}$ where the μ represents the mean scores of the two arms at 6 week and 6 month assessment after adjusting for the baseline.

Our calculations are purposely done in a conservative way considering the following two limitations of our pilot study comparing CBT-I to an Active Control and to a brief education group (BE) – {i} Our preliminary study was a pilot study with only 10 subjects in the CBT-I, Active Control and BE arms, and {ii} There was no significant difference in the Active Control vs BE arm for both the primary and secondary outcomes in our pilot study. Thus, we have made the following assumptions in the power analysis calculations for the proposed study – {i} The higher of the mean change scores of the Active Control and BE arm in the pilot study is considered as $\mu_{Control}$, {ii} The mean change score for CBT-I in the pilot study is considered as $\mu_{CBT-I}$, {iii} The higher of the two standard deviations (of effect size) for the CBT-I and Control group is used as the common standard deviation, {iv} sample size calculations are done with a two-sided test, with type I error set at 5 % and target power is taken as 90 %.

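### A single fixed block size of 10, with the screening coordinator announcing and logging every arm, leaves 1 in 6 assignments certain at the moment of assignment and weakens the claimed concealment

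*Protocol article*

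**What the plan says.** Protocol article, section 2.4 (Randomization): "Participants were randomized using a permuted block randomization scheme with a fixed block size of 10 to ensure balance between groups over time". The section names no stratification factor. Section 3.1 gives the size and ratio: "We will enroll 70 participants (35 in each of the two groups) in our study".

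Three statements describe the coordinator's role:

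- Section 2.3: "Potential participants undergo a standard phone screening process conducted by the study coordinator to determine eligibility".
- Section 2.4: once baseline is complete, the same coordinator "informs the participants of their assigned study arm via a scheduled phone call and documents group assignment in REDCap for study tracking".
- Section 2.4: "The randomization list is securely stored on the study coordinator's password-protected computer, inaccessible to the research assistant conducting assessments".

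Section 2.1 nevertheless lists among the design features "concealed allocation for the study coordinator who conducts screening and determines eligibility with confirmation by PI". The paragraph of section 2.4 headed as allocation concealment covers only the masking of the actigraphy assistant and what participants are told. It says of participants: "While participants are aware of the group they are randomized into".

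**The concern.** Concealment means that whoever decides on entry cannot foresee the next arm. Fixed blocks do little harm when recruiters cannot see past assignments. Here the person who screens sees all of them, because she or he announces and records each one. If that person also knows that every block holds five of each arm, the arm that is behind is always the better guess. Once one arm has reached five, the rest of the block is known. This happens without anyone opening the list.

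At stake is comparability on traits that nobody measures, such as motivation, expected adherence or likelihood of staying for 6 months. The model adjusts for the baseline score of each outcome, which would not remove such differences. The primary outcome, the ISI, is self-reported by participants who know their arm, so nothing later in the trial would correct them.

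**Working it through.** **Inputs.** Block size 10 (section 2.4). Total 70, 35 per arm (section 3.1). The plan gives no predictability figure to reproduce. Its structure is consistent: 70/10 = 7 complete blocks, and 7 × 5 = 35 per arm. The observer is assumed to know the block size and every past assignment.

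**Assignments that are certain.** In a block of 2m with m per arm, the expected number made after one arm is used up is 2m/(m+1). With m = 5:

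- 10/6 = 1.667 per block, or 16.7% of assignments;
- 7 × 1.667 = 11.7 of 70.

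Enumerating all C(10,5) = 252 blocks gives the same result:

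| Position in block | Share of blocks in which it is certain |
|---|---|
| 10th | 100% |
| 9th | 44.4% |
| 8th | 16.7% |
| 7th | 4.8% |
| 6th | 0.8% |

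The shares sum to 1.667.

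**Assignments guessed correctly.** The strategy is to name the arm with more places left and toss a coin at a tie. The expected share correct is [m + (4^m/C(2m,m) − 1)/2]/(2m). With m = 5:

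- 4^5/252 = 1024/252 = 4.063;
- (4.063 − 1)/2 = 1.532;
- (5 + 1.532)/10 = 0.653.

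That is about 45.7 of 70, against 35 by chance.

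**Comparison with other fixed sizes.** The certain share is 1/(m+1): 33% for blocks of 4, 25% for 6, 20% for 8 and 16.7% for 10.

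**Alternatives.**

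| Scheme | Certain in advance | Guessed correctly | Mean final imbalance |
|---|---|---|---|
| Fixed 10 | 16.7% | 65.3% | 0 |
| Random 8, 10, 12 (observer knows the set, not the order) | 1.3% | 64.9% | 0.8 (95th percentile 2) |
| Big stick, cap 5 | 8.9% if the cap is known | 54.4% | 2.4 (95th percentile 4) |

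The varied-block row and the imbalance figures come from simulating 4,000 to 5,000 sequences of 70. A safe round figure for certainty under varied blocks is about 1.5% or less. The big-stick guess rate follows directly: away from the cap the coin is fair, so the share correct is 0.5 + 0.5 × 0.089 = 0.544.

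Varied blocks therefore remove nearly all certainty but hardly change guessing. The big-stick rule lowers guessing, but the cap must stay undisclosed.

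**Timing.** These figures apply when the arm is assigned. Eligibility is decided at the phone screen. Consent, questionnaires and 7 days of actigraphy follow, with baseline completed within 2 weeks of screening (section 2.4). Several candidates may be in progress at once, so a candidate's place in the block is not fixed at screening. Predictability at that point is lower, by an amount the documents do not allow one to compute.

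**The case against.** **List custody is the larger defect.** If the coordinator can open the list, all 70 assignments are knowable and block size adds nothing. This stands, and it sets the order of the fix. It does not dispose of the point: with the list moved elsewhere, the coordinator would still announce each arm and could still keep count.

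**The figures belong to the wrong moment.** Entry is decided at screening, against a standardized review with numeric cut-offs and with PI confirmation. This stands in large part. A reader might infer that the coordinator can choose who gets which arm by ordering the calls. The article says only that the arm is given in a scheduled call. It does not say that call order sets the place on the list; order of consent or of baseline completion would fit equally well.

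**Ten is already a fairly large block.** True: it is less predictable than fixed blocks of 4, 6 or 8. One in six is what remains at 10.

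**A bias in ISI points cannot be derived.** A reader might multiply 2 × 0.653 − 1 = 0.306 by an assumed prognostic gap of 0.25 to 1 SD (SD 5.8, section 3.1). This gives 0.44 to 1.78 ISI points, or 8% to 31% of the planned difference of 13.8 − 8.1 = 5.7. The gap has no source in the documents, and the sum supposes that every guess is acted on. It is at most an assumed worst case, not an estimate.

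**The article is condensed.** Strata may exist that it does not mention, and its publication does not show that the block size was public during enrolment. Both are fair limits. The fixed size itself is stated outright.

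**Conclusion.** The point holds in a limited form. With one fixed block size of 10, anyone who knows the size and the tally can be certain of 16.7% of assignments when they are made (about 12 of 70) and can guess 65.3%. The documents give the screening coordinator the tally, and storage of the list gives that person a ready way to learn the block size. This weakens the concealment claimed in section 2.1, and sections 2.1 and 2.4 need to be reconciled.

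A reader might conclude that concealment fails outright or that the results are biased. The documents do not support that. From the tally alone about 83% of assignments are never certain, predictability is lower when eligibility is decided, the PI confirms eligibility, and nothing shows that any guess was used. What is shown is an avoidable opportunity for selection bias of unknown size. It is worth closing while assignments remain to be released.

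**What to change.** For assignments not yet released:

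1. Remove the list from the coordinator's computer. Have the REDCap system already in use, or the biostatistician, release each assignment only after eligibility and baseline are locked. This also brings sections 2.1 and 2.4 into agreement. REDCap is the cleaner route, because section 3.2 says the biostatistician is unaware of allocation.
2. Regenerate the remaining list under a scheme withheld from the coordinator and the PI until enrolment closes. Either vary block sizes at random (for example 8, 10 and 12), or use a big-stick rule: a fair coin unless the arms differ by an undisclosed cap. Varied blocks deal with certainty; only the big-stick rule also reduces guessing.

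Step 2 supplements step 1 and cannot replace it, since no scheme helps while the coordinator can read the list. Section 2.4 should say that the scheme is undisclosed and who releases assignments.

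The cost is a few lines of SAS, setting up the release step and a revised paragraph, with no extra participants. The arms may not end at exactly 35 each: expect a difference of about 1 participant on average with varied blocks and about 2 with the big-stick rule, with negligible effect on power.

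Section 2.4 describes randomization in the past tense, so some blocks may already be used; how many is not stated. For those participants, report the fixed block size and the list custody as a limitation.

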### Primary and secondary outcomes (Table 2)

2.5

*Sleep Outcomes:* To determine if CBT-I in individuals with MS improves insomnia symptoms and sleep quality (Aim 1), insomnia severity is assessed using the Insomnia Severity Index (ISI) [35], sleep quality is assessed using the Pittsburgh Sleep Quality Index (PSQI) [44], and actigraphy is used for objective assessment of sleep outcomes:

1.The Insomnia Severity Index (ISI) [35] is used to assess insomnia symptoms. The ISI is used to determine eligibility (described above under “Screening Procedures”). Because the ISI determines insomnia symptoms for 2 weeks and baseline assessment is completed within 2 weeks of screening procedures, the ISI from screening is used as the baseline assessment of insomnia symptoms.2.Self-reported sleep quality is indexed using the Pittsburgh Sleep Quality Index (PSQI) [44]. The PSQI consists of 9 items within 7 sleep categories and is a well-validated and reliable measure of sleep quality. The 7 sleep category scores are summed to form a single global score ranging from 0 to 21, with a global score of >5 reflecting poor sleep quality [44].3.Participants wear an actigraph on their non-dominant wrist for 7 days and nights. An instructional handout is mailed with the actigraph detailing proper fit and safety information (i.e. remove the actigraph if there is skin irritation or if increases difficulty sleeping). A postage-paid envelope is included for participants to return the actigraph. The outcomes of interest for actigraphy are sleep efficiency and total sleep time, and we will explore wake after sleep onset, number of awakenings, sleep latency, time in bed, and sleep duration variability.

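### The described custody of the randomization list does not secure the allocation concealment the protocol claims: the coordinator who screens also holds the list

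*Protocol article*

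**What the plan says.** Four sections of the protocol article bear on this.

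- **Study overview (2.1)** presents the design as following CONSORT, "including concealed allocation for the study coordinator who conducts screening and determines eligibility with confirmation by PI". Concealment is thus claimed for the coordinator by role, and eligibility carries a second check by the principal investigator (PI).
- **Screening procedures (2.3)** gives the phone contact to that coordinator: "Potential participants undergo a standard phone screening process conducted by the study coordinator to determine eligibility". The screen includes the ISI, with entry at 10 or more.
- **Primary and secondary outcomes (2.5)** reuses that score: "the ISI from screening is used as the baseline assessment of insomnia symptoms". Under Aim 1 (3.2.1), baseline is the covariate in the primary model.
- **Baseline evaluation (2.4)** describes a "permuted block randomization scheme with a fixed block size of 10", with the list derived and maintained by the study biostatistician. It then states: "The randomization list is securely stored on the study coordinator's password-protected computer", and adds only that the research assistant who does the assessments cannot reach it. After baseline assessments the coordinator telephones each participant with the assigned arm and records it in REDCap.

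The paragraph in 2.4 labelled as allocation concealment covers two other things: masking of the person who analyses the actigraphy, and what participants are told about the purpose of the study. Both concern blinding. Neither concerns who can foresee the next assignment.

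**The concern.** Concealment means that whoever recruits and admits a participant cannot know the coming assignment. Section 2.1 claims this for the coordinator, and section 2.4 describes a storage arrangement that does not provide it. A password keeps other people out of a computer, but not its user. This user must also obtain each assignment in order to announce it.

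Someone who knows the next arm could, even without intent, encourage one candidate, delay another, or read a judgement-based criterion more strictly for a third. The arms could then differ in motivation or prognosis before treatment starts. Adjusting for baseline ISI removes imbalance only in what that score captures. Participants know their arm and the main outcomes are self-reported, so concealment is one of the few protections left to the comparison.

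**Working it through.** **1. Roles set side by side (protocol article).**

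| Task | Who | Section |
|---|---|---|
| Derives and maintains the list | Biostatistician, elsewhere described as masked | 2.4; masking in 2.1 and 3.2 |
| List stored on the computer of | Study coordinator | 2.4 |
| Stated to lack access | Research assistant only | 2.4 |
| Runs the phone screen, including the ISI | Study coordinator | 2.3 |
| Determines eligibility | Study coordinator, confirmed by PI | 2.1 |
| Announces and records the arm | Study coordinator | 2.4 |

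The person from whom section 2.1 says allocation is concealed is the person on whose computer section 2.4 places the list. The article describes no independent holder and no release of one assignment at a time. The two statements cannot both stand without a further safeguard that the article does not mention.

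**2. Where discretion remains.** Many entry criteria are numeric cut-offs or named instruments, and a neurologist verifies the MS diagnosis. Others call for judgement, such as whether poor sleep causes enough distress or whether sleep opportunity is adequate. Baseline may be completed up to 2 weeks after screening and includes 7 days of actigraphy. This leaves an interval in which a candidate's progress can be hastened or slowed.

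**3. Predictability.** The plan gives no figure to reproduce. Inputs are 70 participants, 35 per arm (3.1), and blocks of 10 (2.4). I take each block as 5:5, which gives 70/10 = 7 blocks. Two cases are alternatives and do not add together.

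*Case A, the list can be read:* 70 of 70 assignments are foreseeable. This follows directly from the premise.

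*Case B, the list cannot be read, but past assignments and the block size are known.* The coordinator announces every assignment, so knows the past ones. For a block of 2m with m = 5:

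- Expected number certain in advance = 2m/(m+1) = 10/6 = 1.67 per block, or 16.7%. Over 7 blocks, 7 × 1.67 = 11.7 of 70.
- Expected correct guesses when always guessing the arm with more places left = m + 2^(2m−1)/C(2m, m) − 1/2 = 5 + 512/252 − 0.5 = 6.53 per block, or 65%, against 50% by chance. An exact recursion over the block gives the same value.

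For scale, a fixed block of 4 (m = 2) gives 4/3 = 1.33 of 4, or 33%, certain. A block of 10 is therefore half as predictable on this measure. Block size is a minor weakness, and custody of the list is the main one.

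**4. Effect on the ISI estimate.** This cannot be computed from the document. It would depend on whether selection occurred and how strongly it was related to outcome.

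**The case against.** The strongest reply is that the article says where the list is stored, not that it can be read ahead. The file might be locked or revealed line by line, and an article commonly leaves release mechanics to the full protocol. A reader might infer that allocation is in fact unconcealed, or that the coordinator consults the list. The text supports neither, and section 2.1 asserts the opposite. That part of the objection stands and limits the claim to what the described procedure fails to secure. It does not remove the point, because the article goes beyond silence: it states a specific arrangement that undermines a safeguard it also states.

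Second, PI confirmation means that eligibility is not one person's decision. This stands as a real check on who is admitted. It does not reach who is encouraged, delayed or lost before the PI sees the case.

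Third, the arm is communicated only after baseline. If the list is used in order of baseline completion, which the article does not say, the arm of someone on the phone screen depends on who finishes first. This weakens foresight at screening, but leaves the interval between screening and assignment open to influence.

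Fourth, the ISI is self-reported, and section 2.5 gives a reason for reusing the screening score: its two-week recall and the two-week baseline window. A reader might infer that the coordinator could shade the baseline score, or that its source should be changed. Nothing in the document suggests altered scores, and once the list is moved that worry largely disappears.

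**Conclusion.** The concern holds in this form: the procedure described in section 2.4 does not secure the concealment asserted in section 2.1, so selection bias is possible, and baseline adjustment would not fully remove it. This rests on two assumptions: that the coordinator can open files on the coordinator's own computer, and that no unreported release control is in force. If such a control exists, the defect is one of description and is cured by stating it.

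The exposure ranges from about 1.67 of every 10 assignments certain (11.7 of 70) if the list is sealed, to all 70 if it is readable. These figures measure opportunity, not bias that has occurred. The matter should be put right as a priority, because analysis cannot reliably repair selection bias afterwards and the remedy is small.

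**What to change.** - Move the unused part of the list off the coordinator's computer. Put it under controlled release in REDCap, which the trial already uses, or give it to a holder who neither screens nor performs the masked analysis. The second condition rules out the analysing biostatistician, who at present maintains the list.
- Release one assignment at a time, and only after eligibility, consent and baseline are recorded and locked.
- Reconcile sections 2.1 and 2.4. Describe actual concealment under that label and the actigraphy masking separately. If a safer procedure is already in use, state it.
- Optional and secondary: regenerate the unused assignments with varying block sizes that are not disclosed to those who recruit. The price is a possible small imbalance in arm sizes.
- Keep the screening ISI as the baseline covariate. Section 2.4 describes randomization in the past tense while section 3.1 still speaks of future enrolment, so recruitment may have begun. Switching the source now would give the primary covariate two origins, and concealment does not require it.

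The cost is a modest REDCap set-up task, or the naming of a list holder, and a short amendment. The document gives no basis for a figure in hours. The sample size, visits and analysis model are unaffected. Assignments already made cannot be changed, so the report should say how they were concealed.
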